## Abstract

**Background:**

Stroke is a leading cause of long-term disability worldwide. Persistent lower-extremity motor and somatosensory impairments after stroke commonly limit walking and balance despite rehabilitation. Virtual reality (VR)–integrated robotic rehabilitation may support structured, goal-directed ankle-foot practice; however, evidence for ankle-foot–focused sensorimotor protocols remains limited. In particular, approaches that combine robot-assisted motor training with plantar tactile localization and VR-supported joint position sense training to target plantar sensory and proprioceptive function are scarce.

**Objective:**

This study aims to evaluate the effectiveness of a structured, VR-integrated, robot-assisted ankle-foot sensorimotor rehabilitation protocol compared with a content-matched manual training protocol in individuals with chronic stroke and to examine its effects on clinical and sensorimotor outcomes.

**Methods:**

This is an assessor-blinded, 2-arm, parallel-group randomized controlled trial. Thirty individuals with chronic stroke will be randomized 1:1 to the robot-assisted training group or the manual training group. All participants will receive conventional rehabilitation. In addition, the robot-assisted training group will receive a structured robot-assisted ankle-foot training program integrated with VR and assist-as-needed control, whereas the manual training group will receive the same structured ankle-foot training protocol delivered manually by a physiotherapist. Interventions will be delivered 3 times per week for 6 weeks, for a total of 18 sessions. Total session duration will be time matched between groups at 50 to 60 minutes per session. The primary outcome will be the change in 10-meter walk test–derived walking speed from baseline to 6 weeks. The secondary outcomes will include 2-minute walk test distance, ankle range of motion, joint position sense, plantar tactile sensation, muscle tone, motor performance, static and dynamic balance, and stroke-specific quality of life.

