### Sample Size

On the basis of the post-intervention walking speed values reported by Cho et al, mean 1.22 (SD 0.33) m/s in the robot-assisted ankle muscle training group, and mean 0.84 (SD 0.29) m/s in the control group, the estimated effect size was Cohen *d*=1.21. Using G*Power 3.1 (version 3.1.9.7; Heinrich Heine University Düsseldorf) for an independent samples *t* test, with a 2-tailed α level of .05, 95% power, and an allocation ratio of 1:1, the required sample size was calculated as 19 participants per group. Therefore, the total sample size was revised to 38 participants.

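### The abstract randomises 30 participants and the Sample Size section 38; at 30, the power on the plan's own inputs is 89%, not 95%.

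*Protocol article*

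**What the plan says.** The Methods paragraph of the abstract gives the randomised total: "Thirty individuals with chronic stroke will be randomized 1:1 to the robot-assisted training group or the manual training group". Equal allocation makes that 15 per arm.

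The Sample Size section takes post-intervention walking speeds from a cited study, "mean 1.22 (SD 0.33) m/s in the robot-assisted ankle muscle training group" and "mean 0.84 (SD 0.29) m/s in the control group", and reports that "the estimated effect size was Cohen *d*=1.21". The calculation was made "for an independent samples *t* test", "with a 2-tailed α level of .05, 95% power, and an allocation ratio of 1:1". From this, "the required sample size was calculated as 19 participants per group", and the section closes: "Therefore, the total sample size was revised to 38 participants".

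No other section of the article states a total. The Results section reports that recruitment began in March 2026 and that four participants had been enrolled by 25 March 2026.

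**The concern.** The randomised total is a core design figure, and the article gives it two values that differ by 8 participants (4 per arm). The difference cannot be put down to condensing a longer protocol, because the same article states both numbers as current.

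Two things depend on which is right. First, the 95% power is derived for 38 only. A reader who takes the total from the abstract and the power from the Methods gets a pairing that the calculation does not support. Second, the total is the only numerical end to recruitment in the article: analysis is to begin once all enrolled participants have finished their post-intervention assessment, and that condition names no number. Participants and treating physiotherapists know the allocation. If the trial closed at 30, or went on to 38, it would be hard to show afterwards that the choice had been fixed in advance.

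**Working it through.** **Inputs (Sample Size section).** Means 1.22 and 0.84 m/s; SDs 0.33 and 0.29 m/s; stated d = 1.21; two-sided α = 0.05; target power 95%; 1:1 allocation; independent-samples t test. The totals compared are 38 (Sample Size section) and 30 (abstract).

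**Effect size.** Pooled SD = √[(0.33² + 0.29²)/2] = 0.311, so d = (1.22 − 0.84)/0.311 = 1.223. The stated 1.21 is slightly lower. The difference is small, and both values are carried through below.

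**Power formula.** With n per arm, degrees of freedom = 2n − 2 and noncentrality λ = d√(n/2). Power is the probability that a noncentral t variable with these parameters falls outside ± the two-sided 5% critical value.

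**Reproducing the plan's figure, then applying the abstract's total:**

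| n per arm | total | df | λ (d = 1.21) | critical t | power, d = 1.21 | power, d = 1.223 |
|---|---|---|---|---|---|---|
| 18 | 36 | 34 | 1.21 × √9 = 3.63 | 2.032 | 94.1% | 94.6% |
| 19 | 38 | 36 | 1.21 × √9.5 = 3.73 | 2.028 | **95.2%** | 95.6% |
| 15 | 30 | 28 | 1.21 × √7.5 = 3.31 | 2.048 | **89.2%** | 89.9% |

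Nineteen is the smallest arm size that reaches 95% under either value of d, so the Sample Size section is arithmetically correct. At 30 participants, power is 95.2 − 89.2 = 6.0 percentage points lower. The type II error goes from 100 − 95.2 = 4.8% to 100 − 89.2 = 10.8%, a ratio of about 2.3.

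**Can 30 be derived another way?** For two-sided tests at d = 1.21, power of 80%, 85%, 90% and 95% needs 12, 14, 16 and 19 per arm. None gives 15. A one-sided 5% test needs 16 per arm for 95% power and has 94.4% at 15, but the section specifies a two-tailed test. For 15 per arm to give 95% two-sided power, d would have to be about 1.36.

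**Effect of loss (assumed rates).** The Sample Size section states no dropout allowance, so 10% and 20% are illustrations only. They treat lost participants as contributing nothing. From 30, a 10% loss leaves 27 (14 and 13) and 85.5% power; a 20% loss leaves 24 (12 and 12) and 80.9%.

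**Effect of covariate adjustment (assumed correlations).** The Statistical Analysis section plans an ANCOVA on baseline speed and the two stratification factors. If baseline and post-intervention speed correlate at r, the effective d is about 1.21/√(1 − r²). The residual degrees of freedom at 30 participants are 30 − 5 = 25 (intercept, group, baseline, hemisphere, and one term for the two FMA-LE strata that the eligibility criteria admit).

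| assumed r | effective d | power at 15 per arm |
|---|---|---|
| 0 | 1.21 | 89.0% |
| 0.3 | 1.27 | 91.6% |
| 0.5 | 1.40 | 95.7% |
| 0.7 | 1.69 | 99.4% |

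**The case against.** The strongest reply is that the two numbers do not carry equal weight. The Sample Size section is where the target is derived, and it says the total was revised, which implies an earlier figure that the abstract still carries. On that reading the power claim is correct and one word in the abstract is out of date. This is the likelier explanation, and it limits the damage: the article never attaches 95% power to 30, and there is no arithmetic error in the calculation itself. It does not remove the conflict, because the article nowhere says that 30 is superseded.

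A second reply is that 89% belongs to an unadjusted t test, whereas the primary analysis is an ANCOVA. This also has force: with an assumed correlation of about 0.5 or more, 30 participants would reach 95%. But the article gives no correlation and ties its 95% explicitly to the t test, so the claim as written is not met at 30.

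A third is that selective stopping is unlikely. The outcome assessor is blinded, no interim efficacy analysis is planned, an independent statistician does the analysis, and analysis waits for the last assessment. These safeguards lower the risk, and nothing suggests that recruitment is being run to 30. None of them fixes the number at which recruitment closes.

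Finally, the loss rates are assumptions, and the planned multiple imputation keeps all randomised participants in the analysis. The power figures after loss are therefore indicative only.

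**Conclusion.** The concern holds. The article gives two current, unreconciled totals, 30 and 38, for a trial that is already recruiting. The stated 95% power is correct for 38 (95.2%) and not for 30 (89.2% at d = 1.21, 89.9% at the d implied by the quoted means and SDs). These figures rest on the plan's own test, significance level and effect size, and need no outside assumption. Whether the planned ANCOVA would bring 30 participants up to 95% depends on a correlation that the article does not state. If 38 is the working target, the design is unaffected and only the abstract is wrong. If 30 is, the power statement is wrong.

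**What to change.** Settle on one total and state it in both places while recruitment is at an early stage.

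- If the target is 38, change the abstract to 38 (19 per arm). The Sample Size section can stand.
- If the target is 30, change the per-group number and total in the Sample Size section to 15 and 30, and replace 95% power with about 89% for the t test. If the sponsor prefers to claim the gain from baseline adjustment, state the assumed correlation and its source.

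In either case, check that the ethics, consent and registry texts carry the same number; they were not available for this review. The cost is a text correction, plus a notification if one of those records differs. If 38 is confirmed, neither the design nor the analysis changes.

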**Results:**

This study is funded by the Scientific and Technological Research Council of Turkey (TÜBİTAK) under the 1002-A Rapid Support Program (grant 225S390). Recruitment began in March 2026 and is planned to continue until May 2027. As of March 25, 2026, four participants have been enrolled and are currently receiving the assigned intervention. Data analysis will begin once all enrolled participants have completed post-intervention assessments.

**Conclusions:**

This trial will provide evidence on whether a structured robot-assisted ankle-foot sensorimotor training program offers additional benefit compared with a content-matched manual training protocol in individuals with chronic stroke. The findings may contribute to the development of standardized, individualized, and sensorimotor-oriented rehabilitation protocols for improving walking and balance after stroke.

## Introduction

### Background

Stroke is a global public health problem associated with high rates of physical and cognitive disability [1]. Approximately 15 million people experience stroke each year; of these, 5.5 million die, and 5 million are left with lifelong disabilities. Over the last two decades (1990‐2019), the absolute number of stroke events has reportedly increased by 70%, stroke prevalence by 85%, stroke-related deaths by 43%, and disability-adjusted life years by 32% [2].

Although rehabilitation during the first 6 months (the acute phase) can yield substantial neurological and functional recovery, lower-extremity dysfunction and abnormal gait patterns frequently persist even after walking capacity has been regained, limiting activities of daily living [3]. Post-stroke gait impairments are commonly linked to the interaction of spasticity, muscle weakness, and motor control deficits [4]. In particular, ankle-foot spasticity may lead to deformities that compromise knee, hip, and trunk control and contribute to gait anomalies, such as asymmetry, reduced walking speed, and genu recurvatum [5,6]. Post-stroke somatosensory impairments are also common in the lower extremities, and reduced sensory input can negatively affect motor performance [7-10]. The plantar surface and ankle play a key role in balance by providing somatosensory feedback and enabling rapid postural corrections [7,9]. Plantar sensory deficits have been associated with poorer balance, increased postural sway, inadequate weight transfer, higher fall risk, and gait asymmetry, while proprioceptive impairments are linked to difficulties in motor learning and reduced walking speed [7-10]. Abnormal foot postures may alter plantar pressure distribution and load transfer, providing a rationale for interventions targeting plantar pressure patterns and somatosensory feedback [9,11].

Advances in engineering have accelerated the adoption of robot-assisted rehabilitation [12,13]. Compared with conventional therapy, robotic rehabilitation can deliver higher-dose, intensive, and repeatable practice [14]. Sensor-derived physical data enable objective monitoring of training performance, supporting individualized parameter adjustment [14-16]. Integrating virtual reality (VR) into robotic training may further promote active engagement through interactive, function-focused tasks [12,16].

Lower-limb robots are commonly classified as exoskeletons or end effectors [17]. Although exoskeleton-based gait training may improve global walking outcomes after stroke, evidence regarding its effects on balance and general lower-limb motor impairment remains less consistent [17,18]. Consequently, there is growing clinical interest in distal ankle robots as a targeted option to address ankle-specific impairments and tailor training to individual patient needs [19-21]. Distal ankle robots typically train dorsiflexion-plantarflexion and inversion-eversion to improve ankle control and may support maintenance of ankle mobility, with potential benefits for ankle range of motion (ROM) and proprioceptive function [19,20]. These devices can be delivered in modes ranging from passive stretching or ROM to active-assisted or active training [19,20].

Most ankle robotics studies to date have focused on passive ROM and stretching, primarily evaluating feasibility and effects on joint mobility and muscle-related properties across heterogeneous devices and parameter settings [15,21-24]. In parallel, there has been increasing emphasis on multicomponent programs combining passive applications with active or active-assisted training, with reported benefits for active ROM, strength, spasticity, balance, and gait outcomes [16,22,23]. However, protocols remain heterogeneous in duration, speed, ROM, feedback, and control strategies, and evidence from systematic comparisons with manual or conventional approaches is still limited [15,24]. Moreover, relatively few studies have examined structured control strategies that monitor performance in real time and dynamically adjust task difficulty during active ankle ROM training [16,23].

Robot-based approaches can promote active participation through VR tasks and deliver assistance using an assist-as-needed (AAN) paradigm. Compared with passive, repetition-based practice, these strategies may better support motor learning and cortical reorganization and may enhance neuroplasticity through task-oriented repetition [25,26]. On the basis of this rationale, this study proposes a structured robot-assisted ankle-foot training protocol that combines passive ROM or passive stretching with active or active-assisted ROM training within a single program. Active engagement will be supported using VR-based games and visual feedback, and assistance during the active component will be adjusted in real time according to game performance using an AAN strategy. This protocol aims to standardize both passive and active components while addressing the limited evidence for performance-sensitive, adaptive control during active ankle ROM training. Importantly, plantar somatosensory input is integral to post-stroke balance and gait [9,27,28]. Although vibrotactile stimulation is commonly used to enhance plantar sensation, most studies have focused on stand-alone vibration devices that are not integrated into robotic rehabilitation systems [27,28]. Furthermore, tactile perceptual learning paradigms have been associated with somatosensory cortical coactivation and plasticity [29,30]. However, evidence is lacking for plantar vibrotactile localization training integrated into robot-assisted ankle-foot rehabilitation in people with stroke, despite the presence of tactile mislocalization after stroke [31-34]. Therefore, this study aims to address this gap by structuring plantar vibrotactile sensory training within a robot-assisted, performance-sensitive, and real-time adaptive framework.

### Study Objective and Hypothesis

The primary objective is to compare the effect of structured robot-assisted ankle-foot training versus manual training on walking speed (m/s) derived from the 10-meter walk test (10MWT) in individuals with chronic stroke. The secondary objectives are to evaluate between-group differences in ankle ROM, walking capacity, motor performance, joint position sense (JPS), plantar tactile sensation, static and dynamic balance, muscle tone, and stroke-specific quality of life (QoL).

The primary hypothesis is that the robot-assisted program will yield greater improvement in 10MWT-derived walking speed (m/s) than manual training, which includes comparable ankle-foot sensorimotor training components delivered by a physiotherapist. The secondary hypotheses are that the robot-assisted program will yield greater improvements in 2-minute walk test distance; ankle sensorimotor outcomes (ROM, JPS, and plantar tactile sensation); and muscle tone, motor performance, balance measures, and stroke-specific QoL. Finally, we hypothesize that integrating plantar vibrotactile sensory localization and VR-based JPS training within the robotic protocol will be feasible to deliver in this population, as reflected by session completion or adherence and safety monitoring.

## Methods

### Trial Design

This is an assessor-blinded randomized controlled trial with 1:1 allocation comparing structured robot-assisted ankle-foot training (robot-assisted training group [RTG]) with structured manual ankle-foot training delivered by a physiotherapist (manual training group [MTG]) in individuals with chronic stroke. Manual training was chosen as an active comparator because it includes similar therapeutic targets and training components to the robot-assisted program, but without robotic assistance, VR feedback, or automated sensorimotor control. This design enables evaluation of the added value of the robot-assisted intervention over a clinically relevant manual training approach. The findings of this trial will be reported in accordance with the CONSORT (Consolidated Standards of Reporting Trials) guidelines. This protocol is reported in accordance with the SPIRIT (Standard Protocol Items: Recommendations for Interventional Trials) guidelines (Checklist 1).

### Study Setting

The study will be conducted at Acıbadem Medipol University Regional Hospital (Istanbul, Turkey) and the Living Robotics Laboratory (Department of Electrical and Electronics Engineering, Istanbul Medipol University). Eligible participants will be adults with chronic stroke diagnosed by a physician and meeting the study eligibility criteria. To reach the target sample size, outpatient clinic records will be regularly screened, relevant clinicians will be contacted, and assessment and treatment appointments will be planned flexibly whenever possible.

Interventions will be delivered by physiotherapists with at least 2 years of experience in neurological rehabilitation [35]. Technical setup and device-related adjustments will be performed by engineers, while clinical procedures, participant positioning, safety monitoring, and supervision of treatment parameters will be the responsibility of the physiotherapy team. Outcomes will be assessed by a blinded physiotherapist at baseline (T0) and post-intervention (T1). Recruitment began in March 2026 and is expected to continue until May 2027. The study flowchart is presented in Figure 1, and the schedule of enrollment, interventions, and assessments is shown in Table 1.

**Figure 1. F1:**
[figure not shown]
Flow diagram of the trial. FMA-LE: Fugl-Meyer Assessment–Lower Extremity; MAS: Modified Ashworth Scale; Mini-BESTest: Mini Balance Evaluation Systems Test; MTG: manual training group; ROM: range of motion; RTG: robot-assisted training gTraining Group; SSQOL: Stroke-Specific Quality of Life Scale; TUG: Timed Up and Go.

**Table 1. T1:** Schedule of enrollment, interventions, and assessments.

Study procedures and assessments	Trial period			
	Enrollment		Post-randomization	
Time point	t_i_ to 0	0	T1	T2
Eligibility screening	✓			
Informed consent	✓			
Randomization	✓			
Primary outcome measure				
10-meter walk test–derived walking speed		✓	✓	✓
Secondary outcome measures				
Passive and active ankle range of motion	✓		✓	✓
Fugl-Meyer assessment for the lower extremity	✓		✓	✓
2-minute walk test		✓	✓	✓
Modified Ashworth Scale	✓		✓	✓
Ankle joint position sense		✓	✓	✓
Single-Leg Stance Test		✓	✓	✓
Timed Up and Go Test		✓		
Mini Balance Evaluation Systems Test		✓		
The Semmes-Weinstein Monofilament Test		✓		
The Stroke-Specific Quality of Life Scale		✓		
Interventions				
Robot-assisted training group			●───────────●	
Manual training group			●───────────●	

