### Sequence Generation and Allocation Concealment

Randomization will be implemented using a centralized computer-based system (Study Randomizer; Phase Locked Software) by a research coordinator who is not involved in referral, intervention delivery, or outcome assessment. Stratified permuted block randomization will be used to balance groups according to baseline FMA-LE severity (0‐20, severe; 21‐27, moderate; and 28‐34, mild or good) [36] and affected hemisphere (right or left). Within each stratum, participants will be allocated 1:1 using fixed block sizes (block size=4; final block=2 if required). Following eligibility confirmation and completion of baseline assessments, participant details will be entered into the system, which will automatically generate the allocation. The allocation sequence will be concealed within the centralized system; enrolling and treating personnel will not have access to the randomization lists or assignment order, preventing prediction or manipulation of allocations.

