### Outcomes

#### Overview

Baseline demographic characteristics (age, sex, stroke date, and affected side) will be collected by self-report, and height and weight will be measured. Clinical and physical outcome measures will be assessed by a physiotherapist blinded to group allocation at baseline (T0) and immediately post-intervention (T1, end of week 6) using standardized assessment procedures.

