*Dynamic balance and functional mobility* will be assessed using the Timed Up and Go test. The time (in seconds) required to stand from a chair, walk 3 m, turn, return, and sit will be recorded. Participants may use their habitual walking aids if needed; no manual assistance will be provided. Three trials will be averaged [52]. The Mini Balance Evaluation Systems Test will assess dynamic balance across anticipatory postural adjustments, reactive postural control, sensory orientation, and dynamic gait. Each of the 14 items is scored 0 to 2 (total 0‐28), with higher scores indicating better balance [53,54].

*Tactile perception* will be assessed using the Semmes-Weinstein Monofilament Test. Five monofilaments will be applied to plantar (7 points) and dorsal (2 points) regions; analyses will use changes in the corresponding force (g) values. Participants will be supine with eyes closed. The monofilament will be applied perpendicular to the skin for ~1‐1.5 seconds; 3 repetitions will be performed at each point and responses recorded verbally [55].

*The Stroke-Specific Quality of Life Scale* will be used to assess QoL. The *Stroke-Specific Quality of Life Scale* is a valid and reliable instrument comprising 12 domains and 49 items, covering the physical, functional, and psychosocial aspects of individuals after stroke. Assessments will be conducted in a quiet environment based on participants’ self-reports, with items scored using a 5-point Likert scale. Total scores range from 49 to 245, with higher scores indicating better QoL. The scale will be administered before and after the intervention, and changes in total and/or subscale scores will be used for analysis [56,57].

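### Table 1 conflicts with the text on the assessment schedule: four of ten secondary outcomes have no post-baseline tick, and seven outcomes are ticked at an undefined T2

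*Protocol article*

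**What the plan says.** The text describes two assessments. Study Setting says "Outcomes will be assessed by a blinded physiotherapist at baseline (T0) and post-intervention (T1", and the Outcomes overview times the measures "at baseline (T0) and immediately post-intervention (T1, end of week 6". The Adherence section again uses T1 for the post-intervention assessment, and the Abstract sets the primary outcome as the change in walking speed from baseline to 6 weeks.

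For quality of life, Secondary Outcomes states: "The scale will be administered before and after the intervention, and changes in total and/or subscale scores will be used for analysis". The same section says that the monofilament result is analysed as a change in force. Statistical Analysis plans baseline-adjusted ANCOVA for the continuous secondary outcomes. On the order of events, Sequence Generation and Allocation Concealment says: "Following eligibility confirmation and completion of baseline assessments, participant details will be entered into the system", and the system then generates the allocation.

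Table 1, titled "Schedule of enrollment, interventions, and assessments", has four time columns: an interval up to time 0, time 0, T1 and T2. The first two are headed Enrollment and the last two Post-randomization. The rows "Timed Up and Go Test", "Mini Balance Evaluation Systems Test", "The Semmes-Weinstein Monofilament Test" and the quality-of-life scale are ticked at time 0 only. The primary outcome and the other six secondary outcomes are ticked at T1 and T2 as well as once at baseline. The training bar for each arm starts in the T1 column. Randomisation is ticked in the first column, and the baseline 10-meter walk test in the second.

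**The concern.** A schedule table is what assessors and coordinators tend to work from, and Study Setting sends the reader to this one. Followed as printed, it gives no post-intervention value for four secondary outcomes, and their planned baseline-adjusted analyses could not be run. Those four rows hold the only measures of dynamic balance, plantar tactile sensation and quality of life, each of which is named in the secondary hypotheses.

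The table also blurs the label T1. In the text T1 is the end-of-training visit that carries the primary outcome. In the table T1 is the column where the training bar begins, and it is followed by an unexplained T2. A data file labelled from the table and an analysis written from the text could mean different visits by T1.

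**Working it through.** No stated figure is in dispute here. The check is a row count and a comparison of table with text.

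**Step 1: ticks by row.**

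| Row | Up to 0 | 0 | T1 | T2 |
|---|---|---|---|---|
| Randomisation | yes | | | |
| 10-meter walk test (primary) | | yes | yes | yes |
| Ankle ROM | yes | | yes | yes |
| FMA-LE | yes | | yes | yes |
| 2-minute walk test | | yes | yes | yes |
| Modified Ashworth | yes | | yes | yes |
| Joint position sense | | yes | yes | yes |
| Single-leg stance | | yes | yes | yes |
| Timed Up and Go | | yes | | |
| Mini-BESTest | | yes | | |
| Semmes-Weinstein | | yes | | |
| Stroke-specific quality of life | | yes | | |

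**Step 2: counts.** There are 10 secondary rows: 6 with T1 and T2 ticks and 4 with neither (6 + 4 = 10). So 4/10 = 40% of secondary rows have no post-baseline assessment. The primary row and 6 secondary rows, 7 in all, have 1 baseline + 2 later ticks = 3 occasions, against 2 in the text.

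**Step 3: do the four rows need a later value?** Yes. Quality of life is to be given before and after training. The monofilament result is a change. Timed Up and Go and Mini-BESTest fall under the T0 and T1 rule in the Outcomes overview and under the ANCOVA plan.

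**Step 4: could broken table text explain it?** It is unlikely. Each assessment row keeps its full set of four time cells, and the six secondary rows directly above the four affected ones carry both later ticks.

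**Step 5: would one relabelling repair the table?** It would not.
- If the table's T1 is the start of training and T2 is week 6, the labels contradict the text and T1 becomes an unplanned repeat of baseline.
- If the table's T1 is week 6, T2 is an undefined later visit and the training bar starts at the primary endpoint.
- Under both readings the four outcomes still have no follow-up.

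**Step 6: timing.** Results reports four participants in training on March 25, 2026. Training lasts 6 weeks = 42 days. Without interruption, their T1 assessments fall due no later than about May 6, 2026.

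**The case against.** The text is coherent, and it is the better guide to what was intended. Missing ticks in one table do not show that data will go uncollected. The trial is run by one coordination team that reviews data completeness weekly, the ethics-approved protocol (version 4) is not shown, and the secondary outcomes are declared exploratory. All of this stands, and it makes this an inconsistency to repair, with no proof of lost data.

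Three stronger readings are tempting, and the documents do not support them.

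- A reader might infer that baseline walking speed is measured after allocation, in unblinded participants, so that the ANCOVA covariate is contaminated. The table heads both pre-training columns Enrollment, the first is an interval ending at 0, and the text plainly puts allocation after the baseline assessments. The placement is ambiguous and no more than that.
- A reader might infer that training runs from T1 to T2, so that the table's T1 is a pre-training visit. In the text read from the PDF, the bar sits in the T1 cell with an empty cell after it, and its span is uncertain. What is secure is that it begins in the T1 column, which does not fit a T1 at the end of week 6.
- A reader might infer that the primary endpoint has two definitions. It has one, used consistently in the text. Table 1 attaches no week to T1 or T2.

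**Conclusion.** Table 1 is wrong as printed and conflicts with the text. Two parts need no inference: 4 of 10 secondary rows have no post-baseline assessment although the text requires one, and 7 outcomes are ticked at a T2 that is neither defined nor analysed. Two further parts are weaker but should be cleared in the same correction: the training bar begins at T1, and the randomisation tick precedes the column with the baseline walk test.

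This is an internal inconsistency and not a design choice. The error most likely lies in the table, because the text is consistent throughout on T0, T1 and the order of baseline and allocation. The primary analysis and the sample size are unaffected. The practical risk depends on whether staff work from the table or from the text, which the article does not show.

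**What to change.** Reissue Table 1 so that it matches the text:

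- Tick all outcomes at T0 and at T1, with T1 labelled as the end of week 6.
- Place randomisation after T0.
- Place the training bar between T0 and T1.
- Delete T2, or define it in the text as a follow-up outside the primary analysis.

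Confirm now, for the participants already in training, that assessors are instructed to collect Timed Up and Go, Mini-BESTest, monofilament and quality-of-life data at T1. Where a T1 visit has already passed, record whether these were obtained, since a missed week-6 value cannot be recovered later. Check that the visit labels in the database follow the text.

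The cost is one corrected table and one check with the assessors. If T2 is deleted, no visit is added.
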